### Study procedure

GP and specialist practices were selected from registries maintained by the Association of Statutory Health Insurance Physicians, with an emphasis on colleagues, who already cooperated in previous studies [17, 38]. In addition, all major memory clinics in the federal state of MV were contacted and invited to participate as recruitment centres. Participating GPs and specialists will receive a compensation fee per every participant they recruit. Participants are recruited by trained practice staff at participating practices and memory clinics during regular visits. Participants who self-identify as family caregivers of PwD and meet the inclusion criteria will be informed about the study and invited to participate in the trial by practice staff. Upon written informed consent, participants will be asked to fill out the self-administered needs assessment (baseline) on the tablet-PC while sitting in the waiting room. Informed consent materials are available from the corresponding author on request.

Consenting GPs and specialists aid in the recruitment of participants in the trial. Information about the study will be available in participating GP offices and memory clinics and interested participants will be given a participant information sheet and a consent form. Participating practices will be cluster randomised into either the intervention or control group. Participants in memory clinics will be randomised individually or will be allocated to the group of their GP practice, if that practice is already part of the trial. In both cases, the allocation to the intervention and control group will be approximately 1:1. The allocation of GP practices to intervention and wait-list control group will be computer-generated with a random number generator. Participants will then be allocated based on their GPs’ group. If the participant’s GP is not yet part of the trial, the participant will be randomised individually and the GP practice (including all following participants naming this GP) will then be allocated to this group. For participants who name a GP who is not yet randomised as part of the GAIN trial, allocation concealment will be ensured as the randomisation code will be released when the patient has been recruited into the trial, which takes place after the baseline assessment has been completed. Since this is a trial involving care management, no blinding will take place. Participating centres, participants and researchers will be aware of group allocations.

Informed consent and agreement forms will be obtained. Participating physicians will sign an agreement form and participants will sign an informed consent form. Participants will be informed that their participation is entirely voluntary and that they are free to withdraw at any time; in the event of their withdrawal, any data collected up until that point would be kept by the research team. Participants’ consent forms will be collected in paper form either by the study nurses or the respective practice staff and send to the study centre via post. As part of the consent, participants will be asked to release from confidentiality of their patient data to allow trial relevant access to this information. This includes consent allowing patient and trial relevant communication between participants’ GPs and trial staff. This trial does not involve biological specimens.

Participants who self-identify and meet the inclusion criteria will be invited to participate in the trial and upon informed consent will be given a tablet to complete the baseline assessment. The assessment uses established and valid instruments to assess participants’ medical needs, home care needs, psychosocial needs and needs connected to the caregiver role. Another part of the baseline assessment is based on the patients’ records (i.e. sociodemographic data and ICD-10 diagnoses).

After completion of the baseline assessment, the control group will receive care as usual and the participants of the intervention group will receive the intervention.

The intervention consists of an individualised systematic feedback of unmet needs ascertained in the baseline assessment issued to the treating GP. The feedback contains recommendations for treatment and care and suggests selected interventions regarding the use of care services, medication, social integration and medical treatment from a comprehensive list of intervention modules. Participants in the intervention group will be contacted immediately after recruitment by specifically qualified study nurses.

Follow-up assessments of all outcome measures will be conducted 6 months after the baseline assessment with both groups. The place and time of the assessments will be chosen based on the highest possible convenience of the participants. The progress and documentation of the intervention will be monitored by the study coordination. If required, the study coordination and the PI will make the final decision to terminate the trial. The trial is reported in accordance with the recommended Standard Protocol Items for Interventional Trials [39] and is registered at ClinicalTrials.gov (NCT04037501).

#### Intervention group

The recruitment and baseline assessment will take place in the primary care setting, at memory clinics and practices. The intervention will be administered face-to-face during visits in participants’ homes (at 2 weeks and 6 months post-randomisation, T1 and T6) and by telephone (monthly over a period of four months, T2-T5) (see Fig. 2).

The intervention group will receive a digitally supported care management programme. The basis of this programme is the tablet PC-based CMS. Upon the GP’s judgement, some or all of the CMS-recommendations and possibly further intervention recommendations will be included in the individualised care plan. Both, the assessment results and the GP’s care plan will be used by the study nurses.

The study nurses will schedule appointments for a home visit within 2 weeks post-randomisation. During the home visit, the study nurses re-visit the assessment results and collect more information about the participants’ unmet needs identified, which will then be reviewed with the participants’ GPs.

The home visit is a key component of the intervention as it allows the study nurses to get an overview of the participant’s home environment and surroundings. Given their professional background and knowledge, the study nurses will be able to optimally gear the intervention to the participant and their individual situation.

In between the home visits, the management of participants’ unmet needs are monitored and actively supported by four monthly telephone contacts. In these contacts, the progress of addressing and eliminating the unmet needs identified is discussed and is recorded in the CMS. The study nurses will also assess and record adherence as well as barriers and supporting factors for successfully alleviating caregivers’ unmet needs.

#### Wait-list control group

After the baseline assessment, the wait-list control group will receive usual care for 6 months. At the 6 months follow-up assessment, participants in the wait-list control group will receive their assessment results and intervention recommendations. Participants in the control group will have access to their usual care. In the standard German care pathway, family caregivers, as any patient, may receive general advice and/or treatment from their GPs or specialists if they actively seek it. Regarding their caregiver roles, they can access online information and self-help groups offered by the Alzheimer Society and other health organisations and charities. However, usual care does not normally include any specific or individualised care management programme as evaluated in this trial.

#### Data collection

Data will be collected in GP practices and memory clinics via a tablet PC-based, self-administered baseline assessment as well as by extraction from patients’ records. Six months after the intervention, tablet PC-based structured interviews will be conducted in participants’ homes. All assessments will be standardised using validated and reliable questionnaires. Data will be end to end encrypted and transferred to a central study database.

To record intervention recommendations provided, a success monitoring system enables standardised documentation of the intervention and the process and success of recommendations including their facilitators and barriers.

The study site will make every reasonable effort to retain participants for the entire study period of 6 months. Home visits and telephone contacts will be scheduled at times convenient for the participant. It is estimated that the drop-out rate will be at 30%. Participants are informed that all data collected up until the withdrawal of consent will be kept and used.

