### Study population and selection criteria

Family caregivers are eligible to participate in the study if they are above the age of 18, the caregiver of a PwD living at home, are able to speak German sufficiently to complete the baseline assessment and give written informed consent. Potential participants will be excluded if they are not living in the study region (Federal State of Mecklenburg-Western Pomerania), do not provide written informed consent, are unable to complete the self-administered baseline assessment and/or cannot be interviewed.

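### Caregiver-reported primary outcomes are taken at 6 months by unmasked home interview at a visit that is also an intervention contact: an avoidable risk of differential detection bias

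*Protocol article*

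**What the plan says.** All references are to the protocol article.

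- **Baseline.** Under Study procedure, "participants will be asked to fill out the self-administered needs assessment (baseline) on the tablet-PC while sitting in the waiting room". Data collection agrees: "tablet PC-based, self-administered baseline assessment as well as by extraction from patients’ records". Among those excluded under Study population and selection criteria are people who "are unable to complete the self-administered baseline assessment"; the same sentence also excludes people who cannot be interviewed.
- **6 months.** Data collection: "tablet PC-based structured interviews will be conducted in" the caregivers' homes. Study procedure instead leaves place and time to the participant's convenience. Neither section says who conducts the interview.
- **Blinding.** Study procedure: "no blinding will take place". The reason given is that the trial concerns care management. Centres, participants and researchers all know the allocation.
- **The 6-month contact.** Intervention group: "The intervention will be administered face-to-face during visits in" the caregivers' homes, at 2 weeks (T1) and at 6 months (T6), with four monthly telephone contacts (T2 to T5) between them. Those calls review and record progress on each unmet need. Under Wait-list control group, controls receive their assessment results and recommendations at the 6-month assessment.
- **Analysis.** Statistical analysis takes the 6-month value as dependent variable and the baseline value as covariate. The effect is judged by a one-sided test of the study-group coefficient. The Abstract also mentions within-group analyses.

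**The concern.** Both primary outcomes are what caregivers say about themselves. At 6 months they say it to an interviewer for whom no masking is planned, at an encounter that also delivers intervention content. The two arms reach that encounter with different histories. One has spent months discussing with a nurse whether each need has been resolved; the other has not. Interviewer leniency, or a wish to please a programme that has helped, would lower the count of unmet needs in the intervention arm only. A one-sided test is most exposed to a bias in the direction being tested.

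The stated reason for not blinding explains why caregivers and nurses cannot be masked. It does not explain why outcome recording is neither masked nor separated from intervention delivery.

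The switch from self-completion to interview is a second, smaller matter. It mixes a mode effect into each arm's change from baseline.

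**Working it through.** The plan states no figure on this point, so there is none to reproduce. The check has three steps.

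**1. Is the risk different between arms?**

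| | Intervention | Control |
|---|---|---|
| Baseline mode | tablet, self-completed | tablet, self-completed |
| Planned contact before T6 | one nurse home visit, four calls about needs | usual care |
| 6-month mode | interview, no blinding | interview, no blinding |
| Also at 6 months | face-to-face intervention visit | results and recommendations handed over |

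Mode is the same in both columns. Contact history is not, so any bias from an unmasked interview can differ by arm.

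**2. Does the mode change bias the primary comparison?** Write the 6-month value as Y = a + m + ρ·B + τ·G + e, with B the baseline value, G the group and m a mode shift common to both arms. The shift m is absorbed into the intercept and τ is untouched. A simulation with 176 per arm, m = 0.3 SD and a baseline correlation of 0.5 (both assumed), no clustering and no true effect gave:

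- adjusted group effect 0.002 SD;
- between-group difference in change 0.001 SD;
- within-arm change 0.299 SD (intervention) and 0.298 SD (control).

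The common shift therefore cancels between groups and appears in full in each arm's own change. Adding a shift of −0.2 SD in the intervention arm only, the adjusted group effect became −0.202 SD. A differential shift passes straight into the primary estimate.

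**3. What could a differential shift do to the test?** Inputs from Sample size: 176 per group analysed, mean cluster size 8, ICC 0.1, coefficient of variation of cluster size 0.63, one-sided α = 0.05.

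- Design effect = 1 + ((1 + 0.63²) × 8 − 1) × 0.1 = 1 + (11.175 − 1) × 0.1 = 2.018.
- Standard error of the difference, in SD units = √(2 × 2.018 / 176) = 0.151.
- Rejection rate at zero true effect with a shift b favouring the intervention = 1 − Φ(1.645 − b / 0.151).

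| Assumed b (SD) | One-sided error |
|---|---|
| 0 | 5% |
| 0.05 | 9% |
| 0.10 | 16% |
| 0.20 | 37% |

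Every value of b is an assumption. This calculation ignores any gain in precision from the baseline covariate.

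**The case against.** **Standardised instruments.** The needs count comes from a standardised assessment within the care management system, and the EQ-5D-5L has fixed five-level answers, so the interviewer's room for judgement is limited. That is fair, and it narrows the risk. It does not remove it, because the answers are still given to someone who may know the arm, during an intervention contact.

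**Interviewer not identified.** A reader might infer that the nurse who supported the caregiver also conducts the interview. The text does not say so, and an article may leave interviewer identity and the order of steps to working instructions. The point does not need that inference: it rests on the stated absence of blinding and on T6 being listed as an intervention contact.

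**Change scores.** A reader might infer that the mode switch makes change scores uninterpretable and so undermines the main result. The documents do not support this. The primary model uses the 6-month value with baseline as covariate, and a mode shift common to both arms cancels. What remains is confounded within-group change and a possible loss of precision from a weaker covariate.

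**Direction.** Months of reviewing needs could also make intervention caregivers report more of them. A bias favouring the intervention is the likelier direction, not a certain one.

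**Limits of the remedy.** Caregivers know their arm, so self-completion leaves their own response bias in place. The analysis includes only people with baseline and follow-up values and does not impute, so extra missing items can cost whole participants on top of the expected 30% drop-out. Both objections stand and are carried into the costs.

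**Conclusion.** The point holds as a risk of detection bias. As written, the plan takes caregiver-reported primary outcomes by unmasked interview at a contact that also carries intervention content, after arm-specific contact about those same needs. This risk is avoidable.

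Its size cannot be drawn from the documents. The 16% error rate belongs to an assumed 0.1 SD shift, combined with the plan's own cluster inputs; it should not be read as the trial's actual false-positive rate. I do not express the shift as a share of the detectable difference. Sample size states one SD, whereas its inputs give (1.645 + 0.842) × 0.151 = 0.38 SD, and that discrepancy is a separate matter.

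The mode change does not bias the planned between-group comparison, provided its effect is the same in both arms. It does make within-group change unusable as an estimate of effect.

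**What to change.** At T6, in both arms:

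1. Have caregivers self-complete the needs assessment, EQ-5D-5L, ZBI-7 and LSNS-6 on the same tablet as at baseline, before any review of the care plan or handover of results. Eligibility already required self-completion at baseline.
2. Keep the interview for FIMA and RUD.
3. Where a caregiver needs help, use an existing staff member not involved in that caregiver's support, and record that help was given.
4. Flag the mode for assessments already done by interview and add a sensitivity analysis by mode.
5. Do not interpret within-group change as an intervention effect.
6. Reconcile Study procedure and Data collection on where the assessment takes place.

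**Cost.** This is a change to the visit instruction, using existing tablets and staff. Expect some more missing items, which matters because the primary analysis does not impute; a check for skipped items before the tablet is returned would limit this. Early participants will have been assessed in a different mode. With first participant-in in October 2020 and recruitment planned to October 2021, 6-month assessments run from about April 2021 to April 2022. The protocol version is dated 12 April 2021, so on those dates most assessments could still be covered. Response bias from caregivers knowing their arm remains and should be stated as a limitation.

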#### Quality assurance and safety

A scientific advisory board was installed to ensure a high quality of this trial. This board consists of experts and representatives in the field who will be meeting twice during the trial. The first meeting was held in February 2020 to discuss the design and the implementation of the trial. A second meeting will be held in February 2021 to discuss the first results and to receive feedback and advice on the scientific analysis.

Regular supervision will be provided to the study staff to ensure adherence to the study protocol, to maintain the quality of intervention delivery and to improve methods, knowledge, practice and skills. Using the tablet PC-based CMS will support a degree of standardisation of the intervention.

The data management of this trial is in accordance with the current version of the Data Protection Concept of the Institute for Community Medicine in Greifswald. This concept is approved by the State of Mecklenburg-Western Pomerania’s data safety and freedom of information office. The Data Protection Concept of the Institute for Community Medicine contains specific regulations regarding cooperation with the German Center for Neurodegenerative Diseases (DZNE) at Rostock/Greifswald and other partners.

Demographic and assessment data will be collected in GP and specialist practices as part of a digitally supported system. Only researchers involved in the trial will have access to the trial data. After the completion of the trial, personal data will be deleted and only the anonymised assessment data will be kept. This data will be kept in a password secured place and will only be accessible to the researchers.

The Data Monitoring Committee (DMC) will be a group which has no other involvement with the intervention. Members of this committee will include researchers and healthcare professionals. The committee will safeguard the interests of trial participants and monitor the overall progress, validity, credibility and conduct of the trial.

#### Publication and dissemination policy

The presentation and reporting of the trial will be in accordance with CONSORT guidelines [40]. Dissemination of the research findings will aim to cover as many channels as possible to ensure that participants, carers, healthcare professionals, researchers and the public are informed. Caregiver of people with dementia will be informed via the Alzheimer’s Association and newsletters. Findings will be published in peer-reviewed scientific journals and disseminated at national and international conferences such as the Alzheimer’s Association International Conference (AAIC) and Clinical Trials on Alzheimer’s Disease (CTAD).

### Statistical analysis

The primary between-group comparisons will be based on analysing participants as initially randomised without imputation of missing data. A full analysis plan will be developed prior to completion of data collection and discussed and consented among all research partners.

Descriptive statistics of demographic and clinical data at baseline will be used to examine differences between both groups. The primary statistical analysis will be intention-to-treat (ITT) including all individuals providing baseline and follow-up values of the outcome variables. ‘As randomised’ analyses will be performed, considering outcome data obtained from all participants regardless of protocol adherence.

To investigate whether drop-out after the baseline assessment may be systematic and influences the results, we will run multivariable logistic regressions with drop-out (yes/no) as dichotomous outcome. The study group, sociodemographic variables, and clinical parameters based on the screening will be included as predictors. These analyses will be performed three times for (1) drop-out overall, (2) drop-out due to death and (3) drop-out due to withdrawal of informed consent.

To describe the study sample, appropriate summary statistics such as the mean, standard deviation, median, minimum and maximum for continuous variables and frequencies and percentages for categorical data will be used. The primary analyses will be conducted by using separate generalised linear models to test intervention effectiveness. The main outcome variables at the primary follow-up (6 months post-randomisation) will be the dependent variables. The model specification will correspond to the scale level of the outcome variable under investigation: number of unmet needs and health-related quality of life. The models will be adjusted for age, sex and living situation of the participants. The study group is the predictor of interest (usual care vs. intervention). The baseline value of the primary outcomes will be included as a covariate to reduce residual variance and to account for inter-individual variance at baseline. A positive intervention effect is defined as a significant regression coefficient (one-sided test) of the study group variable. To improve the quality of the regression models, possible interaction effects will be analysed for study group, age group, living situation and clinical parameters as sensitivity analyses.

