### Sample size

The estimated sample size for the study is *n*=504 participants and is based on power calculations with the NCSS programme PASS 2019 [37]. Expecting a drop-out of 30% within the study period, we assume that data of *n*=352 subjects (*n*=176 per group) will be available at the end of the study. Both groups are planned to consist of 22 clusters, each providing *n*=8 participants on average. Thus, we will be able to show a significant difference between the mean numbers of unmet needs in both groups of at least one standard deviation with a power of 80%. In this set of assumptions, the intra-class correlation is set to 0.1. The coefficient of variation of cluster sizes (COV) is 0.63, which allows variance in cluster sizes between 8 and 37. The hypothesis is tested with a one-sided test at a significance level of *α*=0.05.

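### The primary analysis is labelled intention-to-treat but is a complete-case analysis expected to omit about 30% of randomised caregivers; it can be biased if drop-out depends on outcome differently by arm, and no stated analysis would show this

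*Protocol article*

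**What the plan says.** In the protocol article, Statistical analysis:

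- The missing-data rule: "The primary between-group comparisons will be based on analysing participants as initially randomised without imputation of missing data".
- The analysis set: "The primary statistical analysis will be intention-to-treat (ITT) including all individuals providing baseline and follow-up values of the outcome variables". The abstract also describes the primary analysis as intention-to-treat, without qualification.
- The model is a generalised linear model for the 6-month value of each primary outcome, with study group as the predictor of interest and adjustment for the baseline outcome value, age, sex and living situation.
- Drop-out is examined by three multivariable logistic regressions (any drop-out, death, withdrawn consent) on study group, sociodemographic and clinical variables. Their stated purpose includes finding out whether drop-out affects the results.
- The only sensitivity analyses named for effectiveness are interaction effects.
- A full analysis plan is announced for later.

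Expected loss is given twice. Sample size: "Expecting a drop-out of 30% within the study period". Data collection: "It is estimated that the drop-out rate will be at 30" (per cent). The starting point is given as "The estimated sample size for the study is *n*=504 participants".

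**The concern.** An intention-to-treat analysis concerns everyone randomised. The set defined here is restricted to people who have both the baseline and the follow-up outcome, and the primary comparison does not impute. There is one post-baseline assessment, so no repeated-measures likelihood brings the drop-outs back in. A reader who sees the label will assume coverage that the analysis does not have.

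The label would matter less if drop-out were bound to act alike in both arms, but the design gives reasons to doubt that:

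- Allocation is known to participants, centres and researchers.
- Only the intervention arm has the early nurse home visit and the four monthly calls.
- Controls receive their assessment results and recommendations at the 6-month follow-up, which is an incentive to stay.

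The mix of people who leave could therefore differ by arm in a way that is related to unmet needs or quality of life at 6 months. At stake is the size, and with a one-sided test the false-positive rate, of the primary comparison.

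**Working it through.** **Reproducing the plan's figures.** 504 × (1 − 0.30) = 352.8, stated as 352. Clusters give the same: 2 × 22 × 8 = 352. So 504 − 352 = 152 participants are expected to be outside the primary set, and 152/504 = 30.2%.

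**What the drop-out regressions can show.** The 6-month outcome is missing for those who leave, so it cannot be a predictor in these models. They can show whether the drop-out rate is related to arm and to baseline variables. They cannot show whether drop-outs would have done worse, and they do not alter the effect estimate. The protocol states no action if drop-out proves systematic.

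**When the planned model is biased.** Simulation with true effect 0, 30% drop-out per arm and baseline–outcome correlation 0.6 (assumed), fitting the complete-case regression adjusted for baseline:

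| Drop-out mechanism | Estimated effect (SD) |
|---|---|
| Random | 0.00 |
| Depends on baseline, in the intervention arm only | 0.00 |
| Depends on 6-month outcome, same in both arms | 0.00 |
| Depends on 6-month outcome, in the intervention arm only | −0.14 (favours intervention where lower is better) |

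**Size of the bias.** Let p be the drop-out share in an arm, and d the amount by which its drop-outs are worse than its completers, in SD, after adjustment for the model's covariates. Then

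overstatement of benefit = p_I × d_I − p_C × d_C.

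The documents give no value for d, so these are assumptions:

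| p_I, p_C | d_I, d_C | Overstatement (SD) |
|---|---|---|
| 0.30, 0.30 | 0.2, 0 | 0.30 × 0.2 = 0.06 |
| 0.30, 0.30 | 0.5, 0 | 0.30 × 0.5 = 0.15 |
| 0.30, 0.30 | 0.5, 0.5 | 0.15 − 0.15 = 0 |
| 0.35, 0.25 | 0.5, 0.5 | 0.175 − 0.125 = 0.05 |
| 0.25, 0.35 | 0.5, 0.5 | 0.125 − 0.175 = −0.05 |

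**Scale.** The inputs are from Sample size: 176 per arm, mean cluster size 8, intra-class correlation 0.1, coefficient of variation 0.63, one-sided 5% level, 80% power.

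- Design effect = 1 + ((0.63² + 1) × 8 − 1) × 0.1 = 2.018.
- Standard error = √(2 × 2.018/176) = 0.151 SD.
- Difference detectable with 80% power = (1.645 + 0.842) × 0.151 ≈ 0.38 SD.

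The section itself states a difference of 1 SD. Against 1 SD, 0.06 to 0.15 is 6% to 15%. Against 0.38 SD it is about 16% to 40%.

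**Type I error.** The one-sided rate under a bias b is 1 − Φ(1.645 − b/0.151):

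- b = 0.05: about 9%
- b = 0.06: about 11%
- b = 0.15: about 26%

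This standard error allows for clustering but not for the variance removed by baseline adjustment. A smaller standard error would make the inflation larger for the same b.

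**The case against.** The case on the other side is substantial, and much of it stands.

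- *Bias is not shown.* A reader might infer that losing 30% without imputation must bias the effect. The documents do not support that. They say nothing about how drop-outs differ from completers, and three of the four simulated mechanisms give no bias. Overburdened caregivers may leave both arms alike. This stands, and the point is worded conditionally for that reason.
- *Raw gaps overstate the problem.* A gap between drop-outs and completers that the baseline value, age, sex and living situation explain causes no bias. This stands, so d is defined after adjustment.
- *Multiple imputation is not a cure in itself.* With one follow-up, the planned model is already valid when drop-out depends only on its covariates. Imputation improves on it only through auxiliary variables, and if drop-outs do worse given everything observed, ordinary imputation is biased too. This stands. It leaves open whether imputation should be primary, and it is the reason for a delta-adjusted analysis.
- *The analysis plan may deal with it.* It might be inferred that the protocol rules out imputation altogether. It does not: "analysing participants as initially randomised without imputation of missing data" governs the primary comparisons only, and supporting analyses may appear in the plan not shown. But the primary set, its label and the no-imputation rule are already fixed in the protocol, so they are not details left open.
- *The sentence discloses who is included.* True, and the next sentence makes clear that protocol adherence plays no part. That limits the harm but does not make the label correct.

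**Conclusion.** The label is wrong: the primary analysis is complete-case, with about 152 of 504 randomised caregivers expected to be missing from it. That follows from the text and needs no assumption.

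Bias is a possibility. It requires drop-out that depends on the 6-month outcome beyond the model's covariates and that differs between arms in rate or mechanism. The design makes this plausible; nothing in the documents shows that it will happen. Under the assumed one-arm gap of 0.2 to 0.5 SD, the overstatement is 0.06 to 0.15 SD. Under other mechanisms it is zero or of opposite sign. The comparison with 0.38 SD rests on a recalculation. It should not be read as the protocol's own target, which is 1 SD.

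The remaining weakness is that the protocol raises the question of whether drop-out influences the results and answers it with models that cannot tell. This should be changed before the analysis plan is final.

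**What to change.** 1. Call the primary set complete-case (or modified intention-to-treat), here and in the abstract, and state the missing-data assumption under which it is valid.
2. Prespecify an analysis of all randomised participants by multiple imputation, done by arm and respecting clusters. Use as auxiliaries baseline ZBI-7, LSNS-6 and EQ-5D-5L, the diagnoses from patient records, and recruitment route. Make it the primary or at least a key supporting analysis.
3. Add a delta-adjusted analysis in which the shift for drop-outs can differ by arm, to show how large a difference would change the conclusion.
4. State how deaths are handled. The protocol anticipates deaths among drop-outs, and imputing outcomes after death is not automatically meaningful.
5. Keep the drop-out regressions, described as a diagnostic of who leaves.

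The cost is revised wording and modest extra programming. The auxiliaries are already collected at baseline, and data gathered before withdrawal are kept, so no new data are needed. The full analysis plan is due before data collection ends, so these changes can still be prespecified there.
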